#### Recruitment and retention plans

We are recruiting participants from a pool of patients diagnosed with CVLUs scheduled to begin standard care (1–4 layer compression bandage) at the OSU CWC. Because of the known effect of aging on wound healing, the age distribution of CVLU patients at the CWC and participants in our R21 study [25], our target recruitment is 168 patients aged 55–69 years and 80 patients aged ≥ 70 years. The project manager identifies eligible patients by reviewing CWC clinical records. After CWC clinicians present a letter that introduces our team to the potential participants, the project manager provides study details and confirms eligibility of patients interested in participating in the study. After enrollment, the project manager contacts participants every 2 weeks to answer questions and remind them of study visits. The project manager or PI obtains informed written consent from participants at visit 1. Participants are also asked for permission for the research team to share relevant data with people from the university taking part in the research or from regulatory authorities, where relevant. Participants receive $250 after completing the 12-week study; subgroup participants receive an additional $150 after completing visit 5. There is no anticipated harm for trial participation and thus no provisions for post-trial care or compensation.

### Randomization and intervention

After written informed consent is obtained, patients eligible for the study are randomly assigned to either the treatment group or the placebo group by the project manager using the stratified permuted block randomization scheme generated by the study statistician. Precisely, we divide participants in each age stratum (55–69 vs. 70+ years) into permuted blocks of varying block sizes (4 or 8 people/block). Those in each block will be randomly allocated with a ratio of 1:1 to either of the two study arms. Those in each arm will consume softgels of allocated therapy (EPA + DHA or placebo) daily for 12 weeks. Stratified permuted block randomization ensures balanced randomization across age groups and over time. The varied block sizes were chosen to prevent predictability in treatment allocation. The study participants, clinicians, and researchers are blinded as to treatment.

#### EPA + DHA softgels

Three opaque EPA + DHA softgels (J.R. Carlson Laboratories, Inc.; Arlington Heights, IL, USA) will provide a total daily intake of 1.87 g EPA and 1.0 g DHA. This dose/ratio is proposed because EPA has relatively stronger anti-inflammatory properties than DHA [31], and a similar dose/ratio significantly raised EPA + DHA plasma levels and reduced n-6:n-3 ratios in humans after 4 weeks in our pilot work [25]. The Federal Drug Administration reports that ≤ 3.0 g/d of EPA + DHA is safe for public use [32]. At weeks 0, 4, and 8, participants are given one bottle with the ensuing 1-month supply of EPA + DHA or placebo softgels. A 3-month supply of supplements will be supplied at week 12 (visit 4) for those participants that qualify and enroll in the sub-study.

#### Placebo softgels

Three opaque placebo softgels will provide a total daily dose of 2.5 ml of mineral oil (well below therapeutic dose of 10 ml for constipation). Mineral oil is chemically inert, and on ingestion 98% remains unabsorbed in feces. We have used the same placebo dose in prior studies [25, 33]. The EPA + DHA and placebo softgels will be the same in appearance, lemon-flavored and packaged in like bottles (J.R. Carlson Laboratories, Inc.; Arlington Heights, IL, USA).

### Clinical management

#### Monitoring clinic wound treatments

Standard of care for uncomplicated CVLUs in the CWC involves a silver impregnated dressing under a 1–4 layer compression bandage. However, circumstances (e.g., infection) may arise that require a clinician to alter treatment*.* The project manager conducts weekly wound treatment monitoring checks using a standardized checklist to review participants’ clinic records for changes in wound treatments. Any treatment change (e.g.,oral antibiotic) is recorded. We will control for treatment-related variables by considering them covariates as appropriate.

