### Covariates

To address potential confound of variables that may impact inflammation or wound healing [37], we are collecting data on age, sex, tobacco use, comorbidities, perceived stress, and prescribed/over-the-counter medications. We are also collecting data on dietary intake of nutrients that may affect healing (e.g., vitamin C and protein) using a food frequency questionnaire [38]. All instruments being used to measure tobacco use, perceived stress, and dietary intake have been well vetted so data can be compared across studies. We are also determining if wound debridement or adjunct therapies were used between study visits and noting the type of dressing under compression bandaging.

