### Statistical analysis

Congruent with the RCT design of the study, we will conduct an intent-to-treat analysis. We will first use descriptive statistics to check data distribution, identify outliers, guide appropriate data transformation if needed, and summarize sample characteristics. Two-sample *t* tests and Chi-square statistics will be used to check the balance of baseline measures between two study arms. Mixed-effects linear modeling for repeated measures will be used to test the intervention effect on each outcome measure (PMN activation, lipid mediators, inflammatory cytokines, inflammatory cytokine gene expression, percent reduction in wound area, and pain and QoL). In each model, we will include fixed-effects of treatment (EPA + DHA vs. control), time, and treatment by time interaction, adjusting for possible covariates (e.g., lipid-lowering medications) and data dependancy from repeated measures. From the mixed-effects modeling, we will derive the between-group contrast (EPA + DHA vs. control) estimates of change from baseline in outcome variable at each follow-up time point. Multiple comparison adjustment (e.g., Bonferroni adjustment) will be applied to these between-group contrasts to avoid inflated type I error. Logistic regression modeling will be used to analyze wound recurrence. Again, we will estimate between-group difference in the risks of wound recurrence, adjusting for potential covariates and multiple comparison. Lastly, we will use longitudinal mediation modeling [39] to test hypothesized mediating pathways. A significant mediation pathway is indicated if both paths from X (e.g., treatment) to M (mediator, e.g., pro-inflammatory cytokine) and from M to Y (e.g., PMN activation) are statistically significant. Adequate model fit of a mediation model will be indicated with a non-significant Chi-square statistic, comparative fit index, and Tucker & Lewis Index ≥ 0.9, and a root mean square error of appromixation of ≤ 0.08 [40]. The effect of biological sex and its interaction with treatment will also be examined in the regression models. Missing Data. We expect missing data due to non-adherence, loss of follow-up, or lack of data due to healed wounds. We will carefully examine the extent and pattern of missing data. We will use an indicator variable to flag missing data due to healed wounds and incoporate the variable in the missing pattern analysis. Mixed-effects modeling allows for missing at random [41]. If missing completely at random (MCAR) exists, multiple imputation will be used in order to use the optimal amount of information in our analysis. For missing not at random, pattern-mixture modeling will be used [42]. We will also conduct sensitivity analysis to examine the robustness of study findings from different methods. The trial is considered “minimal risk” by the local IRB and therefore no interim analysis or formal plans for stopping the trial are planned. In terms of data and safety monitoring, a Safety Officer (SO) has been selected and approved by the funding agency in consultations with the PI. The SO has no financial, scientific, or other conflict of interest with the trial. The SO meets with the PI twice annually to review study progress, data quality, and participants’ safety.

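### The wording on covariates lets care given after randomisation into the main treatment-effect models, where it could bias the total effect in either direction

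*Protocol article*

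**What the plan says.** Three parts of the protocol article bear on this.

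- **Monitoring clinic wound treatments.** The section notes that "circumstances (e.g., infection) may arise that require a clinician to alter treatment". It continues: "The project manager conducts weekly wound treatment monitoring checks using a standardized checklist", and "Any treatment change (e.g.,oral antibiotic) is recorded". It then closes: "We will control for treatment-related variables by considering them covariates as appropriate". In context, the treatment-related variables are changes in care during follow-up.
- **Covariates.** After listing items such as age, sex, tobacco use and medications, collected to deal with possible confounding, the section adds: "We are also determining if wound debridement or adjunct therapies were used between study visits". Dressing type is recorded too.
- **Statistical analysis.** Each mixed-effects model contains treatment, time and their interaction, "adjusting for possible covariates (e.g., lipid-lowering medications) and data dependancy from repeated measures". The logistic model for recurrence is likewise adjusted for covariates that are not named. Neither sentence limits covariates to values known before randomisation. The section opens: "Congruent with the RCT design of the study, we will conduct an intent-to-treat analysis".

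No section keeps care given during follow-up out of the main comparison or confines it to a sensitivity analysis. Mediation modelling is described separately, with biological examples (a cytokine, PMN activation).

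**The concern.** A variable that arises after randomisation cannot confound the randomised comparison. It can be a consequence of treatment, of the wound's underlying prognosis, or of both. The trial's own hypothesis (end of Background) is that EPA + DHA lowers inflammation and speeds healing. If that is right, the assigned therapy may also change how often a wound needs an antibiotic, debridement or adjunct therapy.

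Two problems follow if such variables enter the main model:

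1. Part of the treatment effect that runs through the care variable is credited to that variable, so the treatment coefficient is no longer the total effect.
2. If care and healing share an unmeasured cause such as wound severity, conditioning on care makes the arms differ in that cause. This can happen even when the care itself does nothing for healing.

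At stake is whether the reported contrast answers the trial's question: what happens to healing when EPA + DHA is added to standard care.

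**Working it through.** **Step 1: timing.** Allocation is at week 0 (Table 1). Weekly record checks and between-visit items come after it. The stated trigger for altering treatment is the clinical course, for example infection. These are therefore post-randomisation variables that respond to how the wound is doing. Dressing type is ambiguous, because it could be a week 0 value.

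**Step 2: the planned effect.** From Sample size: difference 0.16, SD 0.4, AR(1) correlation 0.7 over three visits, Bonferroni for three comparisons, two-sided 0.05, 80% power, 20% attrition.

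- Variance factor for the mean of three visits: (3 + 2(0.7 + 0.7 + 0.49))/9 = 0.753.
- n per arm = 2 × 0.753 × ((z for 0.05/3 two-sided + z for 80%)/0.4)² = 98.6, rounded up to 99.
- 99/0.8 gives 124 per arm, 248 in total. This matches the plan, so 0.16 is the reference effect below.

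**Step 3: care as an intermediate variable.** Let τ be the total effect, p1 and p0 the proportions with a care change on EPA + DHA and placebo, and β the effect of a care change on area reduction. With no shared cause, a model containing the care variable estimates

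τ − β(p1 − p0).

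The document gives none of p1, p0 or β, so **all values below are assumptions**. Power is for 99 per arm at 0.05/3 on the three-visit mean, holding the standard error at its planned value (a simplification).

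| p0 | p1 | β | Adjusted estimate | Power at that value |
|---|---|---|---|---|
| 30% | 30% | −0.2 | 0.16 − 0 = 0.16 | 80% |
| 30% | 20% | −0.2 | 0.16 − 0.02 = 0.14 | 67% |
| 40% | 20% | −0.2 | 0.16 − 0.04 = 0.12 | 51% |
| 40% | 20% | −0.3 | 0.16 − 0.06 = 0.10 | 36% |
| 40% | 20% | −0.4 | 0.16 − 0.08 = 0.08 | 22% |

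The first row shows the condition: with no difference in care between arms, there is no bias.

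**Step 4: care as a marker of unmeasured severity.** This was simulated with 1,000,000 participants per scenario and a within-arm SD of 0.4. A standard normal severity variable raises the chance of a care change and lowers area reduction by 0.1 or 0.2 per SD. In rows marked 'none', the care change itself does not affect healing.

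| p0 | p1 | Severity effect | Effect of care | True effect | Adjusted estimate |
|---|---|---|---|---|---|
| 30% | 30% | 0.2 | none | 0.16 | 0.16 |
| 40% | 20% | 0.1 | none | 0.16 | 0.135 |
| 40% | 20% | 0.2 | none | 0.16 | 0.114 |
| 40% | 20% | 0.2 | −0.2 | 0.16 | 0.07 |
| 20% | 40% | 0.2 | none | 0.16 | 0.21 |
| 40% | 20% | 0.2 | none | 0 | −0.047 |

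The estimate can be too small, too large, or non-zero when the true effect is zero. In every scenario the model without the care variable recovers the true effect to within simulation error.

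**The case against.** The best defence is that the plan does not fix this adjustment. The wording is conditional, the only example in the model description is lipid-lowering medication, and no model is written out with antibiotics, debridement, adjunct therapy or dressings in it. The Covariates section describes what data are collected. A condensed article normally leaves the final covariate list to the analysis plan. Clinicians are also blinded, so care should differ between arms only through the wound's course or side effects.

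Much of this stands, and it rules out three stronger readings.

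- A reader might infer that all these care variables will be in every outcome model. The text does not say so: items are grouped under a heading and are not assigned to models.
- A reader might infer a contradiction with the intent-to-treat statement. That statement is ordinarily about analysing participants as randomised, which covariate adjustment leaves intact. The issue is which effect the adjusted coefficient estimates.
- A reader might take some percentage of the 16 points as the expected loss. The rates and effects used above are assumed, so any such percentage simply returns the inputs.

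What the defence does not remove is the direction given. The text says the trial will control for these variables, directly after describing changes in care during follow-up, and offers only an unspecified test of appropriateness. That is a stated intention and not a detail left out, and an analysis plan that followed it would inherit the problem. Blinding does not help with care that follows the wound's course, because that is the route by which an effective therapy would alter care.

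**Conclusion.** The concern holds in a limited form. The protocol states an intention to control for care given after randomisation, does not limit model covariates to baseline, and does not keep such care out of the main comparison. If that care is affected by the assigned therapy, adjusting for it could bias the total treatment effect in either direction.

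Neither size nor direction can be derived from the document. The span of 0.07 to 0.21 around a planned 0.16 shows what is possible under the assumed inputs and is not an estimate for this trial. If EPA + DHA does not change the care given, this bias does not arise.

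**What to change.** State in Monitoring clinic wound treatments, Covariates and Statistical analysis that:

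- treatment-effect models adjust only for variables fixed at or before week 0, such as the age stratum used in randomisation. Where a covariate is measured repeatedly, as perceived stress is, the week 0 value is used;
- the recurrence model follows the same rule, with the re-randomisation at week 12 as its reference point;
- antibiotics, debridement, adjunct therapies and dressing changes during follow-up are reported by arm;
- these variables enter a model only in the mediation work or in a sensitivity analysis labelled as such.

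The cost is about one sentence in each section. Data collection, clinical care and the sample size of 248 are unchanged. The article reports nine participants enrolled, so at that stage the rule could be set well before outcome data accumulate.

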#### Monitoring adherence

At each study visit, the subsequent month’s supply of softgels (one bottle) and written and verbal directions for consuming/storing softgels are given to each participant. At subsequent study visits, the bottles are collected. The number of softgels remaining in bottles are counted and logged for each participant. The project manager contacts participants every 2 weeks to review instructions and promote adherence. Adherence is verified by measuring EPA + DHA levels in blood plasma at each study visit to assess changes over time.

### Data and laboratory measurements

All data are anonymized and collected using electronic report forms by investigators or trained research personnel at each study visit who are blinded to the study group assignments. Adverse events are recorded (e.g., gastrointestinal upset). Blood and wound fluid samples are collected at each study visit for use in laboratory tests: quantification of fatty acids, lipid mediators, PMN activation, cytokine levels, and cytokine gene expression.

### Wound fluid collection

Wound fluid is collected from unhealed ulcers at each study time point using a standard wound fluid collection protocol [25, 29]. The fluid is collected by the PI experienced in the protocol or CRC nurses trained by the PI. Briefly, after CVLUs are washed with sterile water, a transparent occlusive film (Opsite, Smith & Nephew, UK) is applied over the wound and the leg is placed in a dependent position for approximately 1–1½ hours. While slowly removing the occlusive film and rinsing the wound with 1 ml of sterile saline, the fluid is collected using a 26G × 0.5″ angiocatheter attached to a 3-ml syringe (Terumo Medical, Somerset, NJ, USA). The fluid is transferred into plain collection tubes and analyzed immediately to determine PMN activation or frozen and stored at − 80^°^ C until further analysis.

### Primary outcome measures

The primary outcome measure with respect to the effectiveness of EPA + DHA oral therapy in the treatment of CVLUs is time to complete wound healing. We define complete wound healing as reepithelialization of the total wound surface. The PI who is blinded to treatment assesses this outcome. The area of unhealed ulcers is quantified at each time point in cm^2^ using a single digital camera photogrammetry system [34]. We calculate percent reduction in ulcer area at weeks 4, 8, and 12 compared to week 0 for each participant and averages for each group. Larger percentages indicate greater healing. The second primary outcome measure is PMN activation in blood and CVLU microenvironments. The determination of PMN activation is accomplished using flow cytometry. Additional measures to assess PMN activation in CVLU fluid involve quantifying reactive oxygen species production during “respiratory burst” by PMNs and two PMN-specific protease biomarkers (matrix metalloproteinase-8, human neutrophil elastase). We also measure free fatty acids in plasma and erythrocyte membranes, lipid mediators in plasma and CVLU fluid, and a panel of pro- and anti-inflammatory cytokines in plasma and CVLU fluid. Finally, inflammatory cytokine gene expression in PMNs (neutrophils and monocytes) is measured.

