### Sample size

Sample size was determined to have sufficient power to detect intervention effect on wound healing, the optimal outcome of the study. Using mixed-effects linear modeling for repeated measures, a total of 248 participants (124 per group) are needed to have 80% power to detect an effect size of 0.4 for between-group comparisons in percent wound area reduction. We assumed (1) a first-order autoregressive covariance structure among the three post-intervention repeated measures, (2) a within-subject correlation of 0.7, and (3) an attrition rate of 20% in the sample size calculation. These assumptions are reasonable based on data from our pilot study [25]. The effect size of 0.4 is corresponding to an average of 16% between-group difference in percent wound area reduction with a common standard deviation of 0.4. Our power analysis also applied Bonferroni method to adjust for three comparisons of primary interest (4-week vs. baseline, 8-week vs. baseline, and 12-week vs. baseline). We used the same approach to conduct power analysis for other outcomes. Our sample size will have over 90% power to detect intervention effects on levels of lipid mediators and inflammatory cytokines and PMN activation, which had medium to large effect sizes based on our pilot study [25, 29]. A two-sided significance level of 0.05 was used for all power analyses. Based on OSU CWC data, we will be able to recruit the required number of people (*n* = 248) in the 53-month recruitment period, averaging 4–5 per month.

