## Discussion

Chronic venous leg ulcers are wounds that cause substantial morbidity, disability, hospitalization, and even mortality among older adults [3, 4]. New therapies are needed because prevalence rates for CVLUs are rising and standard topical therapies are often ineffective [7, 8, 43]. The high levels and expression of PMN-derived proteases in fluid and tissues biopsied from CVLUs [44–46, 47], and the significantly higher levels of PMN-derived proteases found in chronic wounds compared with healing wounds [48–50] indicate that sustained high levels of PMN-derived proteases are factors in healing delays. There is a body of evidence that the omega-3 fatty acids contained in fish oil (EPA + DHA) mitigate PMN activation [18, 25, 27, 50, 51]. The main goals of this study are to determine the effects of combination therapy with oral EPA + DHA supplementation and standard compression bandaging on PMN activation, CVLU healing, and CVLU recurrence. The findings from this trial are expected to lead to a new low-risk adjunct therapy to target and reduce the excessive PMN activation involved in CVLU pathobiology, stimulate healing, and lessen the negative impact CVLUs have on QoL.

In this study, we have chosen wound area in cm^2^ and PMN activation in systemic circulation and in the wound microenvironment as the primary endpoints. Persistent PMN activation and the resulting high levels of PMN-derived proteases in wound microenvironments are well correlated with slow healing, while lower levels are associated with faster healing [50]. Therefore, this primary outcome measurement is a logical approach to evaluate the effectiveness of oral EPA + DHA therapy to target a specific biological process linked to CVLUs. In addition, we will assess the potential mechanisms of action of the intervention, (EPA + DHA-derived lipid mediators and pro- and anti-inflammatory cytokines) and the secondary endpoints of pain, QoL, and CVLU recurrence.

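### The declared primary outcome, time to complete healing, has no planned analysis and no stated power: the trial is sized and modelled on percent wound area reduction, and no rule links it to the second primary

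*Protocol article*

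**What the plan says.** In the protocol article, Primary outcome measures states that the effectiveness outcome "in the treatment of CVLUs is time to complete wound healing", and defines complete healing as full reepithelialization, judged by the blinded principal investigator. It goes on to describe ulcer area and its percent reduction at weeks 4, 8 and 12, and then adds: "The second primary outcome measure is PMN activation in blood and CVLU microenvironments".

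Sample size claims "80% power to detect an effect size of 0.4 for between-group comparisons in percent wound area reduction", with 248 participants, and applies Bonferroni to three comparisons, one for each follow-up visit against baseline.

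Statistical analysis says "Mixed-effects linear modeling for repeated measures will be used to test the intervention effect on each outcome measure" and then lists the outcomes in brackets: PMN activation, lipid mediators, cytokines, "inflammatory cytokine gene expression, percent reduction in wound area, and pain and QoL". Logistic regression is assigned to recurrence, and mediation models follow. On multiplicity it says "Multiple comparison adjustment (e.g., Bonferroni adjustment) will be applied to these between-group contrasts to avoid inflated type I error". The contrasts meant are the between-group differences in change from baseline at each follow-up time.

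The Discussion words the choice differently: "we have chosen wound area in cm^2^ and PMN activation in systemic circulation" and "in the wound microenvironment as the primary endpoints".

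**The concern.** Time to complete healing is a possibly censored event time. Percent area reduction is a repeated continuous measure. A treatment could shrink ulcers without closing more of them by week 12, or the reverse, so one cannot stand in for the other. The Statistical analysis section gives models to secondary outcomes such as recurrence, pain and quality of life, but none to the outcome declared primary. Complete healing enters that section only as a reason for missing data.

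Two things are at stake. The declared primary question may go unanswered, or may be answered by a method chosen after the data are seen. In addition, with two primaries and no rule linking them, it is not fixed what result makes the trial positive.

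**Working it through.** **1. The sections side by side**

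| Section | Healing outcome | Method or power |
|---|---|---|
| Primary outcome measures | Time to complete healing (named primary) | None |
| Sample size | Percent area reduction | 80% power, N = 248 |
| Statistical analysis | Percent area reduction | Linear mixed model |
| Discussion | Wound area in cm² (called primary) | None |
| Aim 3 | Reduction in wound area | None |

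The outcome named as primary appears in neither the power calculation nor the analysis list.

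**2. Reproducing the planned 248**

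Inputs from Sample size: difference 0.16, SD 0.4, so d = 0.16/0.4 = 0.4; AR(1) correlation 0.7 over three follow-ups; 20% attrition; two-sided 0.05; 80% power. Per arm, n = 2(z₁₋α/₂ + z₀.₈)² × v / d², where v is a variance factor.

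- Bonferroni (0.05/3), average of the three follow-ups: v = (3 + 2(0.7 + 0.7 + 0.49))/9 = 6.78/9 = 0.753. n = 2(2.394 + 0.842)² × 0.753/0.16, which rounds up to 99. Then 99/0.8 gives 124 per arm, **248** in all.
- One contrast at 0.05, v = 1: n = 2(1.960 + 0.842)²/0.16, which also rounds up to 99, so again **248**.
- One contrast at 0.05/3, v = 1: n = 131, then 164 per arm, 328 in all. This does not match. With 99 per arm its power is about 66%.

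So 248 is a valid figure for area reduction and carries no information about time to healing.

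**3. What 248 would give for time to healing**

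The article states no hazard ratio, event count or healing rate for this trial. As an assumption, take control healing by week 12 as p = 0.40 (Background: nearly 60% unhealed under compression) to p = 0.50 (Background: median 12 weeks for uncomplicated ulcers). Patients analysed: 248, or 0.8 × 248 ≈ 198.

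Under proportional hazards the treated arm heals 1 − (1 − p)^HR, so events E = (N/2)[p + 1 − (1 − p)^HR]. Schoenfeld's formula for 80% power is ln HR = 2(1.960 + 0.842)/√E. Solving the two together:

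| Control healed | N | Treated healed | Events | HR for 80% power |
|---|---|---|---|---|
| 40% | 248 | 57.3% | 121 | 1.67 |
| 40% | 198 | 59.3% | 98 | 1.76 |
| 50% | 248 | 66.8% | 145 | 1.59 |
| 50% | 198 | 68.7% | 118 | 1.68 |

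At HR 1.5 with 40% control healing, power is about 59% (N = 248) or 50% (N = 198).

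**4. Error rate across the two primaries**

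If each is tested at 0.05 and success on either counts: 1 − 0.95² = 9.75% under independence, about 9.1% at correlation 0.5 and 8.3% at 0.7. Bonferroni over three times within each outcome does not cure this: 1 − (1 − 0.05/3)⁶ = 9.6% if all six contrasts are independent.

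**The case against.** An unseen statistical analysis plan may hold a survival model or a multiplicity rule, and an article may leave such detail to it. That has some force for the alpha question. It does not remove the main point: the article itself lists outcomes and models, and that list disagrees with its own statement of the primary. A separate plan would still have to contradict one of the sections.

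Several stronger readings are tempting and are not supported:

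- **Three rival healing primaries.** A reader might infer a free choice among three. The Discussion's wound area in cm² is plausibly shorthand, because area is measured in order to calculate percent reduction, and Aim 3 speaks of reduction in area. The firm conflict is between time to healing and area reduction.
- **A detectable hazard ratio near 1.9.** This comes from applying 40% healing to both arms (0.40 × 198 = 79 events, HR 1.88). The Background figure describes compression therapy, hence the control arm. With a real treatment effect there are more events.
- **A settled 40–50% healing rate.** The Background says that older and larger ulcers heal more slowly, and the eligibility criteria admit ulcers up to 12 months old and 60 cm². The range is an assumption.
- **Healing dated only at study visits.** The article ties area measurement to visits; for complete healing it says only who assesses it.
- **An error rate that is certainly inflated.** The article never says that success on one primary suffices; if both are required, there is no inflation. A figure of 14.3% for three tests (1 − 0.95³) also needs PMN activation in blood and in wound fluid to be separate, independent routes to success, which is not stated.

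The sample size arithmetic is not at fault, and PMN activation does have a stated power above 90%.

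**Conclusion.** The point holds and should be corrected before analysis. The declared primary effectiveness outcome has neither a planned test nor a stated power, while the sample size and the model serve a different outcome. This contradiction rests on the text alone.

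Its size is conditional. Under proportional hazards, 40–50% control healing and 198 to 248 patients analysed, 80% power for time to healing requires a hazard ratio of about 1.59 to 1.76. The article offers nothing to show whether an effect of that size is expected. The family-wise error of up to about 9.8% applies only if either primary alone can carry the trial, and it falls as the outcomes become correlated. What the documents do show is that the rule is unstated.

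**What to change.** Make Primary outcome measures, Sample size, Statistical analysis and the Discussion name the same single healing primary.

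- **Simplest choice:** percent wound area reduction with one pre-named contrast, for example week 12 at two-sided 0.05. Step 2 shows that 99 evaluable per arm, 248 enrolled, gives 80% power for it. This changes the present plan of three Bonferroni-adjusted contrasts and should be stated as a change.
- **Time to complete healing** then becomes a secondary outcome, analysed by a discrete-time or interval-censored model where healing is dated only by study visit. The weekly clinic-record checks now capture treatment changes, so a healing-date item would have to be added if finer dating is wanted.
- **If time to healing stays primary,** add that model to Statistical analysis and state its power with an explicit control healing rate and hazard ratio.
- **PMN activation:** either state that both primaries must succeed, or test it after the healing primary in a fixed sequence at 0.05, with the blood and wound-fluid measures and their time points ordered in advance. Splitting alpha 0.025/0.025 instead would cut power for area reduction to about 72–73%, and 288 to 298 participants would be needed to restore 80%.

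The cost is an amendment to the protocol and registry and one added model. Changing the named primary after enrolment has begun needs a dated justification; the article reports nine participants enrolled. In a fixed sequence, PMN activation is confirmatory only if the healing test succeeds.
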